## **5.2. Study Rationale**

With ACF now becoming mainstream global policy, there is a pressing need to definitively investigate the more promising approaches to community-wide ACF, where costs but also potential benefits are high, and where contemporary examples with impact evaluation have given conflicting results (21,23-27).

With four separate studies showing evidence of population-level effect (21,24-26) the Harare-ACF approach described above already has a relatively strong evidence-base, but has still not been widely implemented in Africa. In part, this reflects the “conditional recommendation” for this type of intervention from the 2013 WHO Guidelines for Systematic Screening for active TB (5), graded as such because of weak evidence at that time:

- no cluster-randomised trials with population-level endpoints had been carried out to evaluate the Harare-ACF intervention (randomised trials are required to qualify as “Strong Evidence” under the GRADE system)
- the only case-finding intervention investigated with a cluster-randomised trial using prevalence survey/TB transmission endpoints (ZAMSTAR) evaluated 2 different interventions in a multifactorial design and found no benefit in the general population enhanced case-finding (ECF) arm, and a relatively small and marginally-significant effect ( $p=0.06$ ) in the “household-contact” arm (27). Unlike the Harare/Blantyre-ACF intervention, no “peak” in TB case-notifications was reported in the ECF arm, suggesting that the intervention (delivered indirectly through schools, facilities, and community hubs such as market places) was either not effective, or did not reach the necessary intensity/coverage to have efficacy at population level.

A cluster-randomised trial result showing an increase in TB case-notifications from a relatively low-cost and replicable ACF strategy would contribute to regional ACF practice, increasing willingness to invest in broader implementation and impact evaluation (22, 28).

### **5.2.1. Symptoms-plus-microscopy as an ACF strategy**

The ACF strategy has notable limitations (29), including low sensitivity, difficulty producing sputum, and prevalence survey findings that only ~50% of individuals with undiagnosed TB in the community report chronic cough. In Harare, only an estimated 20% to 25% of undiagnosed TB cases were found in any given ACF round (21).

Nonetheless, this was sufficient to double case-notifications and substantially reduce undiagnosed TB, with a similar estimated magnitude to for annual Xpert-based screening in Vietnam. Of note, the more pronounced the contribution of behaviour-change component of ACF --- which can contribute more than direct ACF diagnosis in the field (24,30) --- the less sensitive the strategy will be to field-diagnostic performance (31).

Advantages of smear-microscopy are high throughput, low consumable costs (~\$USD 0.50 in Blantyre compared to ~\$23 for Xpert MTB/RIF), low equipment costs, and easy supply chain management and maintenance. Microscopy is still far the most widely used bacteriological test for TB, globally, and also in Malawi. The National TB Programme already supports highly decentralised smear-microscopy, has community collection-points, and has included community-based ACF in urban slums as part of the current NTP strategy.

The other feasible diagnostic strategy would be chest radiography (X-ray), which has high sensitivity and can be combined with a specific confirmatory test, such as Xpert, with or without use of preliminary symptom screening (5,29). Radiography for TB screening is becoming more feasible for low resource settings, with digital images, falling hardware price of, and computer-assisted diagnostics (CAD) that perform as well as expert readers (32,33). Population-based radiological screening is still a major undertaking, requiring substantial capital investment and dependent on adequate road networks (34). Moreover, in Malawi, radiography has not been fully decentralised below District Hospital level, making community-based screening incongruous at the present time (5).

### **5.2.2. Point-of-care TB and HIV diagnostics provided in the ACF intervention**

**HIV counselling and testing:** ACF participants will be offered **oral HIV test kits, with the option of self-testing**. This recognises the high prevalence of undiagnosed or untreated HIV in community-members with cough (35), and the high acceptability, safety and accuracy of community-based HIV self-testing (8,36,37). ACF team members will be trained to support accurate HIV self-testing and to provide brief health information and post-test counselling following an approach developed and optimised in Malawi, and now adopted as part of national HIV programme policy.

For SCALE, ACF participants will be offered the choice of **HIV self-testing (OraQuick® HIV Self-Test)** either at an ACF tent located within the intervention cluster, or at home. Participants self-testing HIV-positive will have confirmatory testing using finger-prick rapid HIV test kits.

Newly diagnosed or untreated PLHIV will be referred to routine services for ART (available at primary care level with same-day initiation in Blantyre).

## 6. RESEARCH QUESTIONS, AIMS AND OBJECTIVES

The **broad objectives** are to investigate whether providing periodic TB/HIV ACF, focused on investigation of chronic cough leads to increased TB case-notifications.

### 6.1. Research Questions

The key research questions are: -

- 1) Does community-wide ACF increase the rate of diagnosis of microbiologically-confirmed TB at primary care clinics? If so
  - With what time-course relative to the ACF visit?
  - Are time trends the same for microbiologically-confirmed and microbiologically-unconfirmed TB?
  - To what extent does increased case-notifications relate to increased demand for TB testing services, rather than direct diagnosis by specimens submitted to the ACF team?
  - In the context of declining case notification rates, what fraction of Blantyre TB transmission is attributable to health facility and HIV care clinic exposure?
- 2) Is delivery of HIV self-testing alongside the offer of TB testing acceptable to symptomatic ACF participants of unknown HIV status?
  - What is the diagnostic yield (number of confirmed new HIV-positive individuals per 100 self-testers) from HIV self-testing provided alongside ACF for TB?

### 6.2. Specific aims

The specific aims are to:

1. To estimate the pre-intervention prevalence of undiagnosed TB in Blantyre, using combined radiological and bacteriological survey of 15,500 adults.
2. To carry out a cluster-randomised trial with 72 clusters (~4,400 adults each) randomised to: enhanced Standard of Care (SOC) arm or intervention (ACF) arm
3. To compare between randomisation arms after 1 round of ACF:-
  - a. Time trends in microbiologically-confirmed TB case notification rates
4. To investigate the broader effect of ACF on health-seeking behaviour
5. To investigate the costs, cost effectiveness, and projected impact of ACF for TB and HIV on underlying TB epidemiology
6. To investigate the fraction of Blantyre TB transmission attributable to health centre and HIV care clinic exposure

## 7. TRIAL DESIGN

SCALE is a cluster-randomised trial of TB/HIV active case-finding with constrained randomization (1:1 ratio) of 72 clusters of ~4,400 adults per cluster, with boundaries defined by community health worker catchment areas

**Figure 1. Original study design.**

[figure not shown]

*Previously undefined abbreviations:* SOC= Standard of Care; k= thousand; mos= months

**Clusters randomised to the ACF intervention arm** will receive 1 round of brief door-to-door enquiry for chronic cough, repeated after 10 months, with staggered cluster initiation over 9 months. Health promotion messaging will be provided at the time of ACF, through leafleting and door-to-door interactions at the time of brief enquiry for chronic cough.

**All clusters (Enhanced Standard of Care):** Irrespective of randomisation, each facility in the study area will be provided with one study staff member (community/environmental health worker) responsible for facilitating identification of attendees with cough for TB investigations and basic infection control; receiving TB or HIV positive clients referred following ACF; and assisting District TB Officers to register patients being investigated for TB, with a special focus on men.

**Outcomes will be evaluated for months 1-3 from ACF initiation** using routine case-notification data for TB case-notification rates.

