|                              | Objectives                                                                                                                                                                                                                                                                                                                                                                                                                                                                                                           | Outcome Measures/Endpoints                                                                                                                                                                                                                                                                                                                                                                                                                                                                               |
| 1 Primary Outcome            | 
To determine the impact of TB-ACF on population-level:
 
2.1 Rates of adult registration for microbiologically-confirmed TB
                                                                                                                                                                                                                                                                                                                                                                              | 
To compare between randomisation arms:
 
1.1 The rate of treatment (per 1000 adult residents per year) during the 3 months starting from the first ACF intervention, defined by entry into the District Health Office TB Treatment Register and laboratory records
                                                                                                                                                                                                                           |

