Recent TB prevalence surveys including 11 African countries, provide the first regionally representative data since the 1960s (16,17). These confirm the same key findings first reported from subnational surveys in South Africa and Zimbabwe (18,19). Meta-analysis of 86 surveys with 3.1 million participants shows (16): -

- much higher than anticipated rates of undiagnosed infectious TB --- the main driver of TB transmission --- prompting 2 upward revisions of WHO Global TB estimates
- men and urban residents at disproportionately high risk of undiagnosed TB
- prolonged infectiousness before diagnosis or death (median 2.6 years for men and 1.6 years for women) as deduced from comparison with case-notification data
- most survey participants with undiagnosed infectious TB being HIV-negative, even in African countries.

In Malawi and neighbouring Zambia, 2013/14 prevalence surveys report 901 and 993 culture-positive participants per 100,000 urban adults screened, respectively (16), with approximately 2.4 undiagnosed TB cases for every case diagnosed in any given year in Malawi. However, the pre-intervention prevalence survey conducted as the first phase of this study has initial

results showing only 200 confirmed TB positive participants per 100,000 urban adults screened.

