### 9.1. Primary and secondary outcomes

The **primary outcome** will compare between arms

1. **The rate of treatment for microbiologically-confirmed TB (per 1000 adult residents per year) during 3 months starting from the first the ACF intervention**, defined by entry into the District Health Office Electronic TB Treatment Register and laboratory records, with cluster resident status of registering TB patients defined by Global Positioning System (GPS) coordinates for place of residence captured by a satellite map application (ePAL) in routine use by Blantyre District TB Officers.

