| 1. Primary Outcome                              | 
To determine the impact of TB-ACF on population-level:
 
2.1 Rates of adult registration for microbiologically-confirmed TB
                                                                                                                                                                                                                                                                                 | 
To compare between randomisation arms:
 
2.1 The rate of treatment (per 1000 adult residents per year) during the 12 months starting from the first ACF intervention, defined by entry into the District Health Office TB Treatment Register and laboratory records
                                                                                                                                                                                                                                                                                               |
| 3 Other pre-planned analyses                    | 
To investigate the impact of TB-ACF on population-level:
 
3.1 Demand for routine TB testing services
 
To determine the impact of provider-initiated HIV self-testing for TB-ACF participants on:
 
3.2 Numbers of newly diagnosed HIV-positive participants, and numbers subsequently linking into HIV care
 
3.3 Numbers of participants diagnosed with TB using sputum microscopy
 | 
To compare between randomisation arms:
 
3.1 The rate (per 1000 adult cluster residents p.a.) of investigation for TB, defined by entry into the “Presumptive TB Register” in selected routine TB Registration Facilities
 
Within clusters randomised to the ACF-arm only, to document rates (per 1000 adult cluster residents p.a.) of:
 
3.2 New diagnosis of HIV made by the ACF team using OraQuick, with follow-up for confirmatory testing and ART initiation
 
3.3 New diagnosis of TB made by the ACF team using microscopy
 |

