### 13. ECONOMIC EVALUATION

The main objective of the economic evaluation is to estimate the affordability and cost-effectiveness of the TB/HIV ACF intervention with the main focus being the TB intervention.

Specifically, we will estimate the incremental cost-effectiveness of ACF in comparison to facility-based case-finding only. To achieve this, inputs (costs) and outputs will be estimated.

Effectiveness data will be provided by:

1. Numbers of additional patients started on TB treatment, both a) following detection of undiagnosed patients by the ACF and b) as evidenced by differences between trial arms in notification rates identified through the Blantyre District Electronic TB Register (“additionality”)
2. Numbers of **new TB cases** and **TB deaths** averted as estimated from fitting an established HIV and TB model (13) to pre-intervention and post-intervention survey data and case-notifications.

Key outputs will be:

1. Incremental costs per additional individual started on TB treatment (using both direct diagnosis by the ACF team and additionality capture by the Electronic TB Register)
2. Incremental costs per DALY, new TB case, new TB infection and TB death averted

Two economic evaluations will be undertaken: firstly, a within trial evaluation; and secondly, projection a fully-costed dynamic transmission model. Both will be used to estimate the expected incremental cost per disability-adjusted life year (DALY). The mathematical model will estimate TB infection, case and TB death averted. For each analyses, the perspective will be that of the provider, and will only include the direct intervention and medical costs.

The within trial evaluation will adopt a time horizon matching the length of intervention in the trial, with no need to discount costs or DALYs given that the intervention is brief. The model-based evaluation will adopt a 20 year horizon, with future costs and DALYs discounted at 3.5%, and sensitivity analysis to explore alternative discount rates.

The primary analysis will focus on the direct intervention and the broader healthcare costs. This will include the costs of TB and HIV screening, the costs incurred in linking participants to TB/HIV services and any associated staff costs.

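### The primary window is 3 months in most places and 12 in others, and no other between-arm analysis after month 3 is planned to separate earlier from additional diagnoses

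*Combined protocol and SAP*

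**What the plan says.** **Window.** Section 7 says "Outcomes will be evaluated for months 1-3 from ACF initiation". Section 9.1 defines the primary outcome as a rate "per 1000 adult residents per year) during 3 months starting from the first the ACF intervention", the synopsis says "during the 3 months starting from the first ACF intervention", and the abstract agrees. The synopsis gives follow-up as one to three months per cluster. The objectives table in section 9.1 instead says "during the 12 months starting from the first ACF intervention", and the power statement in section 14.1 also assumes 12 months of follow-up.

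**Intervention.** Section 10.4.2 describes one visit of one to two weeks per cluster. The abstract and specific aim 3 also refer to one round. Section 7 says one round but, in the same sentence, mentions a repeat after 10 months.

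**Questions asked.** Section 6.1 asks "With what time-course relative to the ACF visit". Aim 3a in section 6.2 is a between-arm comparison of "Time trends in microbiologically-confirmed TB case notification rates".

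**Use of the difference.** Section 13 takes additional patients started on treatment partly from direct ACF detections and partly "as evidenced by differences between trial arms in notification rates identified through the Blantyre District Electronic TB Register". It does not say how many months after the visit enter that difference. It ties the within-trial horizon to the length of the intervention, which does not settle the matter.

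**Still open.** Section 14.2 leaves the detailed analysis plan to be written.

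**The concern.** A brief door-to-door visit draws on a stock of undiagnosed cases. Notifications should rise soon after it. Some of the patients found would have been notified later in any case, so a fall below the control arm could follow. Section 5.1.2 also raises the opposite possibility, a lasting change in health-seeking. Neither can be seen by month 3.

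Three things are at stake:

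- The size of the effect depends heavily on the window, and the documents do not settle which window defines it.
- A 3-month difference, or the same difference stated per year, could be read as a yearly gain.
- If section 13 uses that difference, the cost per additional patient treated could look too favourable.

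**Working it through.** **1. The plan's own figure.** Section 14.1 gives about 150,000 adults per arm, 12 months, a control rate of 70-100 per 100,000 per year, k = 0.3-0.4 and a detectable increase of 44-56%. With 72 clusters there are 36 per arm, so y = 150,000/36 ≈ 4,167 person-years per cluster. Alpha and power are not stated; two-sided 0.05 and 80% are assumed here. The formula is

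c = 1 + (z_α/2 + z_β)² × [(λ0 + λ1)/y + k²(λ0² + λ1²)] / (λ0 − λ1)².

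Solving for λ1/λ0 with c = 36:

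| Control rate per 100,000, k | 12 months | 3 months (y/4) |
|---|---|---|
| 100, k = 0.3 | 44.0% | 84% |
| 70, k = 0.4 | 56.7% (55.7% without the +1 term) | 106% |

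The stated range is therefore reproduced with 12 months and not with 3. Power for a 44% increase (rate 100, k = 0.3) falls from 80% to 36%. Power for a 56% increase (rate 70, k = 0.4) falls from 79% to 38%. No gain from adjusting for pre-intervention rates is included.

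**2. One round read over two windows.** The interim survey figure in section 5.1.1 is 200 undiagnosed per 100,000 adults. Section 5.2.1 cites 20-25% of undiagnosed cases found per round in Harare.

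- Undiagnosed cases in one arm: 200/100,000 × 150,000 = 300.
- Extra cases: 0.20 × 300 = 60 to 0.25 × 300 = 75.
- Expected control cases over 12 months: 105 to 150. Over 3 months: 26.25 to 37.5.
- Rate ratio over 3 months: 1 + 60/37.5 = 2.6 to 1 + 75/26.25 = 3.9.
- Rate ratio over 12 months, none brought forward: 1 + 60/150 = 1.40 to 1 + 75/105 = 1.71.

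The arm size cancels out of these ratios.

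**3. Allowing for earlier diagnosis.** Let f be the share of extra cases that would have been notified later in the same year. Then the 12-month ratio is 1 + (extra/control) × (1 − f). The documents do not give f, so the full range is shown:

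| f | 12-month ratio |
|---|---|
| 0 | 1.40-1.71 |
| 0.5 | 1.20-1.36 |
| 1 | 1.00 |

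The 3-month ratio is the same in every row. That is the sense in which the short window cannot separate earlier from additional diagnosis.

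**4. The unit.** Per year: 60/37,500 to 75/37,500 person-years = 1.6-2.0 per 1000 per year. Gained over the round: 60/150,000 to 75/150,000 = 0.4-0.5 per 1000 adults.

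**The case against.** Much can be said on the other side, and several stronger readings that a reader might infer are not supported.

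- *Outcomes are read only in months 1-3.* The objectives table and section 14.1 say 12 months. This is an unreconciled contradiction, not a settled choice.
- *The time-course question cannot be answered.* Registrations go into a continuous register (section 10.5.1), so timing within 3 months can be described and later months retrieved. What is missing is a specified analysis.
- *Stating the rate per year biases the result.* It does not change the rate ratio. It affects only how the absolute difference is read.
- *The endpoint is wrong.* Section 6 asks whether ACF increases notifications, and the primary outcome measures that. A short window may also suit a concentrated rise: the illustrated ratio of 2.6-3.9 exceeds the 1.84-2.06 detectable at 3 months. Hence this point does not argue against a 3-month primary window as such.
- *Most extra cases are merely early.* Section 5.1.1 quotes "prolonged infectiousness before diagnosis or death (median 2.6 years for men and 1.6 years for women". Under an exponential assumption, 1 − 2^(−0.75/2.6) = 18% and 1 − 2^(−0.75/1.6) = 28% would reach diagnosis or death in the next 9 months. If all were diagnoses, the 12-month ratio would be about 1.3-1.6. Patients who would have died undiagnosed are truly additional. These durations are pooled from many surveys, so the result is indicative only.
- *Section 13 uses the annualised difference.* It does not say so. It is unspecified, not shown to be wrong.

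The gap itself stands: outside the conflicting 12-month entries, no between-arm comparison after month 3 is described, and section 13 has no window for its additional patients.

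**Conclusion.** The concern holds as a gap in specification that is cheap to close. On the documents' figures, the same 60-75 extra cases read as a ratio of 2.6-3.9 over 3 months and 1.4-1.7 over 12 months, and lower still if some were only brought forward.

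This illustration assumes that the Harare yield carries over, that all cases found are confirmed and registered within 3 months, and that a cluster has one round. It leaves out cases arising from changed health-seeking, which section 5.2.1 says can contribute more than field diagnosis.

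The power figures rest on the assumed alpha and power, and on k being the same for both windows. They show that the stated detectable increase belongs to 12 months. They do not show that a 3-month analysis must fail.

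**What to change.** 1. Reconcile the 3- and 12-month windows across the abstract, synopsis, section 7, section 9.1, the objectives table and section 14.1. State that the 44-56% figure belongs to 12 months, and that power for those effects is about 36-38% at 3 months.
2. Reconcile the one round and the repeat after 10 months in section 7 with section 10.4.2. A second round would fall inside a 12-month window.
3. Define an index date for standard-of-care clusters, which the plan does not give, for example from the staggered start schedule. Any month-by-month comparison depends on it.
4. Whichever window is primary, pre-plan a between-arm analysis of confirmed notifications by month, for 12 months before and 12 months after the index date, from the same GPS-coded register. Report the cumulative 12-month difference.
5. Report any 3-month result also as cases per 1000 adults over the 3 months.
6. In section 13, base the arm-difference count of additional patients on the cumulative 12-month difference.

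**Cost.** Wording and analysis time, with no new data collection. The register has run since 2011 and continues. Clusters started by March 2020 reach month 12 by March 2021, before funding ends in August 2021. The downside is that the longer-window effect will look smaller and is more exposed to migration between clusters.
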